# Localising occult prostate cancer metastasis with advanced imaging techniques (LOCATE trial): a prospective cohort, observational diagnostic accuracy trial investigating whole–body magnetic resonance imaging in radio-recurrent prostate cancer

**DOI:** 10.1186/s12880-019-0380-y

**Published:** 2019-11-15

**Keywords:** Magnetic resonance imaging, Prostate cancer, Radiotherapy, Brachytherapy, Recurrence, Positron emission tomography, Cost comparison, Cost-effectiveness, Economic evaluation

## Abstract

**Background:**

Accurate whole-body staging following biochemical relapse in prostate cancer is vital in determining the optimum disease management. Current imaging guidelines recommend various imaging platforms such as computed tomography (CT), Technetium 99 m (^99m^Tc) bone scan and ^18^F-choline and recently ^68^Ga-PSMA positron emission tomography (PET) for the evaluation of the extent of disease. Such approach requires multiple hospital attendances and can be time and resource intensive. Recently, whole-body magnetic resonance imaging (WB-MRI) has been used in a single visit scanning session for several malignancies, including prostate cancer, with promising results, providing similar accuracy compared to the combined conventional imaging techniques. The LOCATE trial aims to investigate the application of WB-MRI for re-staging of patients with biochemical relapse (BCR) following external beam radiotherapy and brachytherapy in patients with prostate cancer.

**Methods/design:**

The LOCATE trial is a prospective cohort, multi-centre, non-randomised, diagnostic accuracy study comparing WB-MRI and conventional imaging. Eligible patients will undergo WB-MRI in addition to conventional imaging investigations at the time of BCR and will be asked to attend a second WB-MRI exam, 12-months following the initial scan. WB-MRI results will be compared to an enhanced reference standard comprising all the initial, follow-up imaging and non-imaging investigations. The diagnostic performance (sensitivity and specificity analysis) of WB-MRI for re-staging of BCR will be investigated against the enhanced reference standard on a per-patient basis. An economic analysis of WB-MRI compared to conventional imaging pathways will be performed to inform the cost-effectiveness of the WB-MRI imaging pathway. Additionally, an exploratory sub-study will be performed on blood samples and exosome-derived human epidermal growth factor receptor (HER) dimer measurements will be taken to investigate its significance in this cohort.

**Discussion:**

The LOCATE trial will compare WB-MRI versus the conventional imaging pathway including its cost-effectiveness, therefore informing the most accurate and efficient imaging pathway.

**Trial registration:**

LOCATE trial was registered on ClinicalTrial.gov on 18th of October 2016 with registration reference number NCT02935816.

## Background

Prostate cancer (PCa) is the leading male cancer in the United Kingdom and a principal cause of cancer-related mortality with around 46,700 cases diagnosed in 2014 [1]. The incidence of PCa has increased markedly over the past 20 years and it is projected to rise by 12% between 2014 and 2035 to 233 per 100,000 males [1]. Common treatments options for localised prostate cancer are external beam radiation therapy (EBRT), brachytherapy (BRT) or radical prostatectomy [2].

However, biochemical recurrence (BCR) following radiotherapy occurs in 25% of treated men within 5 years, manifesting as a rising prostate-specific-antigen (PSA) [3]. This is strictly a biochemical diagnosis, most commonly defined as an increase in serum PSA of 2.0 ng/ mL above the nadir [4]. Once a PSA relapse has been diagnosed, it is important to determine whether the recurrence has developed at local or distant sites and hence BCR following therapy often initiates an imaging-based assessment of local and metastatic disease in patients.

Local recurrence of PCa is investigated by prostate multi-parametric magnetic resonance imaging (mp-MRI) [5] whilst metastatic disease is assessed by multi-modality imaging. The standard workup to detect PCa metastases usually includes ^99m^Tc bone scan and chest/abdomen/pelvis (CT-CAP) scan (or where available ^18^F-choline or ^68^Ga-PSMA PET-CT) [6].

The workup to exclude distant metastasis is of greatest significance as it is estimated that about half of those who develop radio-recurrent disease have distant metastases (either overt on imaging or micro-metastases) [7]. It is also believed that up to 50% of men who are considered to be free of metastases by conventional staging methods have micro-metastatic disease [8]. This is reflected in prostate cancer recurrence following EBRT or BRT, where biochemical relapse commonly precedes clinical detection of metastases by an average of 7–8 years [9].

Earlier detection of metastatic disease could be the key to better patient stratification and well-informed patient management either by opting for active surveillance or local salvage for low risk individuals or offering systemic therapy at an earlier time point to a high-risk population [10].

Recent technological advances have enabled the reliable whole-body MRI (WB-MRI) staging of cancers within a reasonable scanning time (less than 1 h) [11–14]. There is a clear need for an imaging modality that is capable of improved sensitivity for metastatic disease detection than current conventional imaging [15–17]. Previous meta-analysis has reported the sensitivity of ^99m^Tc bone scan to be less than 50% [18]. Similarly, studies have shown the sensitivity of ^18^F-choline PET to be as low as 50% for the detection of nodal disease when PSA is < 5 ng/ml [19]. Furthermore, CT Scan sensitivity for nodal disease detection in prostate cancer is reported to be much lower with a meta-analysis reporting a sensitivity of 30% [20].

The LOCATE study investigates the diagnostic performance of WB-MRI for detection of nodal and metastatic disease compared to current standard multi-modality imaging comprising ^18^F-choline PET-CT and ^99m^Tc bone scan (+/− CT-CAP) in patients with the radio-recurrent PCa.

### Study objectives

#### Primary objective

To compare the diagnostic accuracy of WB-MRI for regional lymph node and distant metastatic disease detection against an enhanced reference standard of ^18^F-choline PET-CT (or CT CAP) and ^99m^Tc bone-scan for men presenting with BCR following EBRT or BRT.

#### Secondary objectives

Inter-observer agreement of WB-MRI for regional lymph node and distant metastatic disease detectionDerivation and evaluation of apparent diffusion coefficient (ADC) and fat fraction (FF) signal heterogeneity indices of metastatic disease as predictors of treatment response to ADTExploration of the significance of the Human Epidermal growth factor Receptor (HER) activated dimer in metastatic castration-resistant prostate cancerCost-effectiveness of WB-MRI for radio-recurrent prostate cancer staging compared with conventional imaging modalities

## Methods/design

### Study design

The comparative diagnostic accuracy study will conform to the Standards for Reporting of Diagnostic Accuracy (STARD) statement [21]. The study is a prospective cohort multi-centre diagnostic study where all participants will have WB-MRI and conventional imaging tests (^18^F-choline PET or CT-CAP and ^99m^Tc bone scan) with findings of both validated against an enhanced outcome-based reference standard. The patient recruitment flowchart is illustrated in Fig. 1.

**Fig. 1 Fig1:**
[figure not shown]
Trial flowchart. The trial flowchart describing the standard of care pathway through which patients were reviewed and clinical decisions made. A parallel research pathway was designed to mimic the standard pathway without interfering in patient care except when clinically significant incidental findings are identified

### Sample size

Based on 50% prevalence of metastases, 130 patients will be required to demonstrate a minimum of a 20% difference in sensitivity for detection of metastases on a per-patient level between WB-MRI and combination of ^18^F-choline PET-CT and ^99m^Tc bone scan (power of 90% and statistical significance cut-off of 0.05).

### Ethical approval

The LOCATE trial received UK Research Ethic Committee (REC) approval from the National research ethics service (NRES) Committee London-Chelsea with REC reference 15/LO/0776 and will be conducted in accordance with the principles of ICH guidelines on good clinical practice in clinical trials and the Research Governance Framework for Health and Social Care (England).

### Recruitment

#### Inclusion criteria

Men who have undergone previous EBRT or BRT with or without neo-adjuvant/adjuvant hormone therapy.

Biochemical relapse as determined by increase in PSA.

#### Exclusion criteria

Men unable to have MRI scan, or in whom artefact would significantly reduce quality of MRI.

Men unable to give informed consent.

#### Informed consent

In all cases, patient information sheets and sample consent forms will be made available to patients a minimum of 24 h prior to the consent procedure. Consent will be obtained at the time of the appointment and prior to commencement of any trial intervention.

### Trial interventions

#### Whole body MRI

Recruited patients will have WB-MRI scan on presentation with BCR and then at 12 months (follow-up). All WB-MRI scans will be performed at University College London Hospital NHS foundation trust (UCLH) imaging department on a 3.0 T scanner (Ingenia; Phillips Healthcare, Best, Netherlands), using a fixed protocol (Table 1). For participants’ comfort, the WB-MRI protocol will be limited to a maximum of 1-h scan time.

**Table 1 Tab1:** Whole Body MRI sequence parameters

	T2-TSE	mDixon (pre- and post-contrast)	DWI (b0, 1000)
Slice orientation	Transverse	Coronal	Transverse
Echo time (ms)	80	2.303	17
Repetition time (ms)	1214.69	3.5	6304.5
Space between slices	5.5	2.5	5.5
Number of slices	40	120	40
Slice thickness (mm)	5	5	5
Acquisition matrix	500*497	240*238	124*118
Echo train length	89	2	39
Number of averages	1	1	2
Pixel bandwidth (Hz)	538	1847	3354
Pixel spacing	0.78/0.78	1.04/1.04	2.08
Flip angle	90	15	90

*TSE* Turbo spin echo, *DWI* Diffusion weighted imaging

#### Conventional imaging

Recruited patients will have the standard imaging investigations according to local and national guidelines as below:

#### Multi-parametric prostate MRI

A standard prostate mp-MRI protocol as defined by the UK consensus guidelines on prostate MRI [22] will be used to locally stage prostate cancer. Conventional T1 and T2-weighted images of the prostate will be supplemented with diffusion weighted imaging (DWI) MRI (as per hospital site protocol); and +/− dynamic contrast enhanced (DCE) T1-weighted images.

#### Computed tomography

CT scans of the chest/abdomen/pelvis will be performed with intravenous contrast agent using the local standard protocols.

#### ^99m^Technetium bone scan

Bone scans will be performed using ^99m^Tc labelled diphosphonates administered through intravenous injection. For prostate cancer patients with suspected bone metastases, the standard protocol employed at the hospital site will be used. As a guide, whole body imaging will be conventionally performed with anterior and posterior views, 256 × 1024 matrix and energy window(s) of 140 KeV.

#### Positron emission tomography-computed tomography (PET-CT)

^18^F-choline PET-CT will be acquired using a dedicated combined PET/64-detector-CT (VCT-XT Discovery, GE-Healthcare Technology, Chicago, Illinois), CT will be performed (for attenuation correction) using 64 × 3.75 mm detectors, a pitch of 1.5 and a 5 mm collimation (120 kVp and 10 mA in 0.8 s). Maintaining the patient position, a whole-body choline PET emission scan will be performed and cover an area identical to that covered by CT [23].

### Non-imaging trial interventions

#### Blood samples

Blood samples will be taken from recruited patients, by an appropriately trained member of the trial team, at the time of each WB-MRI (staging and then at 12-month follow-up). Blood samples will be used for exosome and phenotypic [Fluorescence-activated cell sorting (FACS) analysis] / DNA-RNA analysis. In total a maximum of 30 ml of blood will be taken:

#### Up to 3 acid citrate dextrose solution (ACD) tubes: to collect ~ 15 ml blood for serum separation

Up to 3 ethylenediaminetetraacetic acid (EDTA) containing tubes for peripheral blood mononuclear cells (PBMC) isolation and further FACS analysis, functional assays, and DNA/RNA isolation.

Frozen aliquots-samples will be transported by courier service in dry ice-containing carrier boxes within 24 h after obtaining the blood sample. Samples will be processed at University College London (UCL) and King’s College London (KCL) laboratories:

UCL: Exosome purification and analysis. Protein-DNA-RNA isolation and analysis.

KCL: PBMC’s isolation, FACS analysis and functional assays.

### Health economic data collection

Data collection for the health economic analysis will be primarily concerned with cost data associated with the diagnosis and treatment of metastatic prostate cancer. Routinely collected administrative data from UCLH will be used to determine the relevant costs associated with the diagnostics test. To determine the consequence of detected metastatic disease on the treatment pathway, clinical experts will be interviewed, and patient notes will be reviewed noting changes to medication, radiotherapy, surgery, outpatient visits, inpatient visits and day cases, where possible. Data from existing trials such as STAMPEDE [24] and FORECAST [7] will be used to inform other economic parameters such as the health-related quality of life as these are not being collected in LOCATE.

### Reporting of trial imaging

#### Initial WB-MRI scan

The study will be reported by two experienced radiologists, blinded to all other imaging investigations, initially independently and then in consensus using a locked sequential read paradigm (LSR). The images will be reviewed for the presence of nodal (N) and metastatic (M) disease and each radiologist will record the presence/absence of disease on the study-specific proforma.

The initial WB-MRI read results will not be revealed to the clinical team. Where a significant additional/incidental finding is demonstrated this will be reported as per standard clinical practice and relayed to the clinical team.

A 1–6 Likert scale [23, 25] will be used for scoring as has been previously described for WB-MRI studies. 1 – disease definitely not present, 2 – probably not present, 3 – possibly not present, 4 – disease possibly present, 5 – probably present and 6 – definitely present.

Scoring will be conducted based on evaluation of imaging features of lymph nodes and bone metastases as indicated below in Table 2 .

**Table 2 Tab2:** Features suggestive of adverse and benign changes in both nodes and bones

	Benign features	Adverse features
Node	Lymph node <5 mm in short axis diameter (SAD) with no concerning features on DWI, T2 weighted or contrast enhanced imaging and definite benign features e.g. (i) Fatty hilum, (ii) Oval nodal morphology with clearly defined and (iii) Regular nodal border and contours.	Concerning features could be described as (i) Size above normal limit e.g. > 10 mm for most, (ii) Loss of fatty hilum, (iii) Irregular border, (iv) Asymmetric high DWI signal intensity, (v) Low T2 signal
Bone	Normal appearing bone with uniform moderate-high signal on T1 weighted imaging and low-moderate signal on T2 weighted imaging. Focal lesions demonstrating clearly incidental/benign multiparametric signal characteristics and/or location	(i) Increase in DWI high b-value signal vs. background noise. (ii) Low signal intensity on T1 and (iii) Intermediate to high signal intensity on T2 (iv) Lesional contrast enhancement

*DWI* Diffusion weighted imaging

#### 12-month follow-up WB-MRI

The study will be reported by the same pair of radiologists who reported the baseline scans. The findings on the follow-up study will be compared with the baseline WB-MRI with access to all conventional imaging. The presence of changes in size of lesions evident on the baseline WB-MRI and/or resolution of lesions evident on baseline WB-MRI will be recorded. Any discrepant findings will be reviewed, and the status of these lesions will be determined in a consensus panel review.

### Derivation of enhanced reference standard

Figure 2 illustrates the derivation of a per-patient level enhanced reference standard (ERS).

**Fig. 2 Fig2:**
[figure not shown]
Enhanced reference standard derivation flowchart. FN: False Negative, TP: True Positive, FP: False Positive, TN: True Negative, UK: Unknown, ADT: Androgen Deprivation Therapy

Patients will be divided into those with and without metastases evident on conventional imaging. For those with metastases (left arm of Fig. 2), concordant positive WB-MRI findings will be deemed to be true positive and discordant WB-MRI findings will be considered to be false negative.

For patients without metastases on conventional imaging (right arm of Fig. 2), clinical and biochemical follow-up together with changes between baseline and follow-up WB-MRI will be used to enhance the reference standard.

Where baseline WB-MRI was negative and concordant with conventional imaging, the presence of new lesions (at follow-up WB-MRI ± repeat routine imaging) coupled with a PSA rise over the 12-month will classify the baseline WB-MRI as false negative, i.e. disease was present but not visualised. Whereas the absence of new lesions regardless of PSA status over the 12-month follow-up period will confer baseline WB-MRI true negative status.

For positive findings on baseline WB-MRI discordant with conventional imaging, the baseline WB-MRI will be deemed true positive when a new lesion declared itself (on follow-up WB-MRI ± routine imaging) or the visualised lesion on baseline WB-MRI enlarged (on follow-up WB-MRI); and this was accompanied with a PSA rise within the 12-month follow-up period. Whereas, the baseline WB-MRI will be deemed false positive when the lesion evident at WB-MRI resolved or reduced in size at follow-up (in the absence of systemic therapy) regardless of PSA change. Lesions that resolved following systemic therapy (which is initiated in the 1-year follow-up period irrespective of negative conventional baseline imaging) with corresponding decrease in PSA will be classified as true positive.

Finally, patients with negative baseline conventional imaging with discordant lesion and PSA changes over the 12-month follow-up (i.e. lesion size/number increase without corresponding PSA increase) will be classified as unknown.

The section below describes the thresholds for PSA and lesion size changes, and they will be interpreted in the context of treatment intervention and subsequent treatment response or progression.

PSA progression defined as ≥25% and ≥ 2 ng/mL increase in PSA recorded at least 12 weeks from baseline or start of treatment and confirmed on a 2nd reading 3–4 weeks later as previously defined [26, 27].

PSA response defined as ≥50% decline from baseline or start of treatment and confirmed on a 2nd reading 3–4 weeks later [28, 29].

Nodal size change Increase of ≥2 mm and decrease of ≥3 mm in short axis diameter on contrast enhanced mDixon sequence will be considered true change (progression and response respectively) rather than a measurement variation, with a 95% confidence interval. (Based on unpublished data from repeatability studies carried out as part of the LOCATE trial).

Bone lesion (disease progression) ≥ 25% increase in size (sum of short and long axes diameters) of lesions on CT, or MRI [30, 31].

Bone lesion (treatment response) ≥ 50% decrease in size (sum of short and long axes diameters) of lesions on CT/ MRI or normalisation of signal intensity on MRI [30, 31].

Soft tissue lesion size change (disease progression) At least a 20% increase in size of lesion taking as reference the baseline diameter of the lesion [32].

Soft tissue lesion size change (treatment response) at least a 30% decrease in the size of lesion, taking as reference the baseline diameter or disappearance of the lesion [32].

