The economic evaluation will also take into consideration the accuracy of WB-MRI versus conventional standard imaging techniques. Specifically, we will model the consequences, in both costs and effects, of true positives, false positives, true negatives and false negative outcomes. Thus, the economic study will evaluate both clinical and economic consequences of the novel imaging technique.

Cost-effectiveness will be calculated as the mean cost difference between WB-MRI versus conventional imaging divided by the mean difference in outcomes (as measured quality-adjusted life years; QALYs) to give the incremental cost-effectiveness ratio (ICER). Also, a cost-consequence analysis will be performed by calculating the mean incremental costs per incremental gain (or loss) in clinical natural units, for example cost per metastases identified.

Finally, to address uncertainty in our clinical and economic parameters, we will perform a comprehensive set of sensitivity analyses on our model estimates. Probabilistic sensitivity analysis using non-parametric bootstrapping methods will be performed. Outputs from this will inform a cost-effectiveness acceptability curve, which shows the probability that WB-MRI is cost-effective at different values of the NHS’ willingness to pay for an additional QALY. We will also subject the economic model to extensive one-way sensitivity analysis to identify key parameters that drive cost-effectiveness.

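### The reference standard accepts every positive conventional scan as true disease without outcome follow-up, so a conventional false positive cannot be recognised and a correct negative WB-MRI in that man is scored as a miss

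*Protocol article*

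**What the plan says.** Study design states that all participants have both WB-MRI and conventional imaging, "with findings of both validated against an enhanced outcome-based reference standard".

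Derivation of enhanced reference standard then sorts men by the comparator's own result: "Patients will be divided into those with and without metastases evident on conventional imaging". Men with metastases on conventional imaging form the left arm in Fig. 2, and the rule there is: "concordant positive WB-MRI findings will be deemed to be true positive and discordant WB-MRI findings will be considered to be false negative". The text gives this arm no false-positive, true-negative or unknown outcome. For men without metastases on conventional imaging (right arm), "clinical and biochemical follow-up together with changes between baseline and follow-up WB-MRI will be used to enhance the reference standard". The unknown category is likewise confined to men negative on conventional imaging.

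The Primary objective compares WB-MRI "against an enhanced reference standard of ^18^F-choline PET-CT (or CT CAP) and ^99m^Tc bone-scan". Sample size plans that "130 patients will be required to demonstrate a minimum of a 20% difference in sensitivity for detection of metastases on a per-patient level", WB-MRI against choline PET-CT plus bone scan, with 90% power at 0.05. The Health economic analysis adds: "we will model the consequences, in both costs and effects, of true positives, false positives, true negatives and false negative outcomes".

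**The concern.** The powered question is whether WB-MRI is more sensitive than conventional imaging. The comparator's positive result by itself makes a man reference-positive, so conventional imaging can never be wrong when it is positive. If such a man is in truth free of metastases, he enters the sensitivity denominator as a success for conventional imaging and, when WB-MRI correctly reads him as negative, as a failure for WB-MRI. Conventional sensitivity goes up, WB-MRI sensitivity goes down, and a real advantage of WB-MRI is understated.

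The Study design section sets the opposite intention. The Discussion describes follow-up as a guard against overcalling by WB-MRI and does not mention overcalling by conventional imaging.

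**Working it through.** **1. The planned sample size.** "Based on 50% prevalence of metastases", 130 men give 65 diseased. The discordance ψ and the two sensitivities are not stated. With the paired (McNemar) formula, two-sided α 0.05, 90% power and d = 0.20:

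n = (1.96√ψ + 1.2816√(ψ − d²))² / d²

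ψ = 0.26 gives n = 64.04, rounded up to 65 diseased, so N = 130. Other inputs do not match (ψ = 0.30 gives N = 150), and an unpaired calculation of 75% against 95% also gives 65. The figure of 130 is thus attainable but cannot be confirmed. ψ = 0.26 is used below as an assumption.

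**2. Can another section make a conventional scan false positive?**
- *12-month follow-up WB-MRI*: records change or resolution of lesions seen on baseline WB-MRI. A lesion seen only on conventional imaging is outside that. The consensus panel there is not tied to the left-arm rule.
- *Reporting of conventional imaging*: double reading and consensus, but no outcome check.
- *Comparison of conventional imaging with WB-MRI*: discrepancies are reviewed and categorised, and WB-MRI accuracy is recalculated after correction. No rule makes a conventional-positive man reference-negative.
- *Discussion*: concedes the lack of histology in general terms.

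None does.

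**3. Size of the effect.** Assumptions:
- 65 diseased and 65 disease-free men.
- True sensitivities 80% (WB-MRI) and 60% (conventional). The measured difference does not depend on their level, only on the 20-point gap.
- Among the diseased, 23% positive on WB-MRI only and 3% on conventional imaging only (ψ = 0.26, d = 0.20).
- WB-MRI negative in 90% of conventional false positives.
- Right arm classified without error.

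With conventional specificity Sp:
- conventional false positives F = 65(1 − Sp)
- reference-positive men n = 65 + F
- WB-MRI true positives = 52 + 0.1F
- conventional true positives = 39 + F
- WB-MRI-only cell b = 0.23 × 65 = 14.95
- conventional-only cell c = 0.03 × 65 + 0.9F = 1.95 + 0.9F
- measured d = (b − c)/n and ψ = (b + c)/n
- power = Φ[(d√n − 1.96√ψ)/√(ψ − d²)]

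| Sp | F | n | c | WB-MRI | Conventional | Difference | Power |
|---|---|---|---|---|---|---|---|
| 100% | 0 | 65 | 1.95 | 80.0% | 60.0% | 20.0 | 0.90 |
| 98% | 1.3 | 66.3 | 3.12 | 78.6% | 60.8% | 17.8 | 0.81 |
| 95% | 3.25 | 68.25 | 4.875 | 76.7% | 61.9% | 14.8 | 0.62 |
| 90% | 6.5 | 71.5 | 7.8 | 73.6% | 63.6% | 10.0 | 0.32 |

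The planned advantage is 0.20 × 65 = 13 men, so 13 conventional false positives with a negative WB-MRI would cancel it.

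**4. If both tests are falsely positive.** Both score a true positive and both sensitivities rise. The difference still shrinks, but little: with 6.5 such men, 13/71.5 = 18.2 points.

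**5. The right arm can pull the other way.** Suppose 6 conventional-only false positives are accepted in the left arm and m false-positive WB-MRI scans are wrongly confirmed in the right arm. The measured difference is (13 − 6 + m)/(65 + 6 + m): 9.9 points for m = 0, 16.9 for m = 6 and 21.0 for m = 10.

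**The case against.** **Direction.** A reader might infer that the whole comparison is biased towards conventional imaging. The protocol does not support that. In the right arm, follow-up WB-MRI, read by the same pair of radiologists, helps to adjudicate the baseline WB-MRI, and a new lesion with a PSA rise can confirm a baseline positive. Step 5 shows that this can offset the left-arm effect or exceed it. The objection stands. It does not repair the left arm, since two errors of unknown size cannot be relied on to cancel.

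**Primary objective.** Its wording could be read as making the comparator the reference standard, which would fix conventional sensitivity at 100% and make a 20-point advantage impossible. The Abstract answers this by building the standard from all initial and follow-up investigations, and the derivation section lets conventional-negative men be reference-positive. This is loose wording to be aligned.

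**Size.** The protocol states no conventional specificity, and its Background discusses only low sensitivity. At 98% the loss is modest. The table is therefore a range under assumptions.

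**Economics.** A reader might infer that the economic model will carry no false-positive costs for conventional imaging. The protocol says that false positives will be modelled and does not say where conventional specificity will come from. All that follows is that it cannot come from this rule.

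**No neutral verifier.** Histology for discrepant cases is ruled out as not feasible. A lesion seen only on conventional imaging has no baseline WB-MRI measurement, and repeat conventional imaging is not scheduled for everyone. Calling the scan false because follow-up WB-MRI is still negative would make WB-MRI its own reference. This stands and limits the fix.

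**Conclusion.** The point holds for the left-arm rule. As written, it contradicts the Study design section, makes conventional specificity 100% by construction, and counts a correct negative WB-MRI as a false negative whenever the conventional scan was falsely positive. This rule alone reduces a true 20-point difference by roughly 2 to 10 points across conventional specificities of 98% to 90%.

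Confidence is high for the mechanism and for the direction of this one rule. The size rests on the assumed specificity, the 26% discordance and the 90% share of WB-MRI-negative men. The net bias of the full standard cannot be determined from the protocol. Fig. 2 is not shown, so the finding rests on the text that describes it.

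**What to change.** 1. Reconcile the Primary objective, Study design and Derivation of enhanced reference standard. State the primary comparison as WB-MRI and conventional imaging, each against the enhanced standard.
2. Adjudicate conventional-positive/WB-MRI-negative men with the 12-month data already planned: PSA course, repeat routine imaging where done, follow-up WB-MRI and treatment context. Allow *conventional false positive* and *unknown* as outcomes. Do not declare a conventional scan false positive only because follow-up WB-MRI is still negative.
3. Report the primary comparison under the current rule and under the adjudicated rule, with unresolved men in this cell counted first as diseased and then as not diseased.
4. State that conventional specificity cannot be estimated under the current rule, and do not feed the economic model from it.

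**Cost.** A change of wording and re-adjudication of one discordant cell. The 12-month WB-MRI is planned for all recruited men, and Study status says full analysis had not begun.

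**Downside.** Some men, mainly those treated after the conventional scan, will stay unresolved. Excluding them is not neutral, because it removes WB-MRI misses. If conventional specificity is perfect and the whole cell of 1.95 men is dropped, 20.0 points become 14.95/(65 − 1.95) = 14.95/63.05 = 23.7. The bounds can therefore be wide. At specificity 95% with the whole cell unresolved, they run from 14.8 points (all diseased) to 14.95/(68.25 − 4.875) = 23.6 points (none diseased), with the true 20.0 between them. Men falsely positive on both tests remain unverified, but their effect is small: at specificity 90% they number 0.65, and 13/65.65 = 19.8 points.
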